#### Valuation of costs

Once the utilisation of services has been established, we will estimate the unit cost of each service. This involves sourcing a value for each item (eg, annual cost of employment multiplied by proportion of time spent), as well as an allocation factor (eg, annual facility head count) allowing the estimation of a unit cost (cost of employment×proportion of time/headcount). These sources of data and allocation factors are outlined in detail in table 1.

For capital items, costs will be estimated using the replacement value method.^37^ In essence, the current replacement value of each items is calculated and annuitized using data on the estimated useful life of the item and an interest rate representing the opportunity cost component for capital, in order to estimate an equivalent annual cost. An estimated useful life of between 5– and 20 years for furniture and buildings will be applied as while an interest rate of 8% will be used as the annuitization factor based on the rate of return on government bonds in South Africa.^37^

### Estimating costs for the patient perspective

#### Measurement of resource use

For the patient perspective, we will use a questionnaire at baseline, 6 and 12 months to estimate resource use. This will capture any user fees associated with public, private or NGO-provided health services as well as traditional and faith-based therapies. In addition, we will ask patients to estimate their time spent accessing healthcare services, as well as out-of-pocket payments for transport, subsistence and accommodation. Travel, subsistence and accommodation costs will relate to both the patient and their caregiver, if the patient is accompanied by a caregiver to any of these services.

#### Valuation of costs

Travel, subsistence and accommodation costs will be estimated using the out-of-pocket payments reported by patients. Time spent receiving healthcare will be valued using the equality of wages approach.^45 46^ We will apply this method as public health services in South Africa are typically accessed by those who have a lower socioeconomic status. Using this technique, the time costs for all patients are valued at the average income reported by the survey population.^45^ This approach is expected to provide a relatively accurate reflection of the opportunity cost of unpaid labour and is favoured over the minimum wage approach in this context as a large proportion of the patients are unemployed resulting in a possible overestimate of the value of the time loss if the minimum wage is used.^45^ In addition, we will ask patients if they have lost any income through seeking healthcare.

Figure 2 summarises the intervention arms, costs and outcomes that will be included in this study.

**Figure 2 F2:**
[figure not shown]
Project MIND: intervention arms, costs, outcomes and economic evaluation. HbA1c, haemoglobin A1c; OOP, out-of-pocket; TAU, treatment as usual.

All costs will be valued at 2017/2018 prices and, to allow comparability with other studies will be converted from South African Rand (ZAR) to US$, using appropriate conversion rates for the same period obtained from OANDA, an online currency exchange rate conversion site. Costs incurred during earlier periods (such as manual development) will be inflated using the Consumer Price Index to reflect 2017/2018 prices.

### Analyses

#### Statistical analysis of costs and effects

Mean provider costs and patient costs will be calculated from baseline until the end of the intervention period. In addition, we will explore the extrapolation of costs to later periods if data allow for this. Cost differences between the MIND-TAU, and the MIND-DES and MIND-DED alternatives will be calculated. Sampling uncertainty for cost data will be estimated using statistical methods that account for the non-normal distribution of costs. Effect in terms of CES-D, AUDIT, HIV viral load, HBA1c and the QALY will be analysed using linear regression on intervention type.

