### Trial design

This study is nested in Project MIND, a cluster randomised controlled trial across 24 public primary care facilities.^24^ Myers *et al*
24 describe the trial in detail. The trial will compare the effectiveness of treatment as usual (MIND_TAU) and two alternative methods for integrating a psychosocial intervention into the primary care services for HIV and diabetes. Treatment as usual (TAU) is representative of typical primary care level services for CMD in the South African public health service facilities, which is typically limited to referrals.^25 26^ The two models will be the dedicated and designated models of care. In the dedicated approach (MIND_DED), community health workers (CHWs) will be hired and added to the facility staff complement and will dedicate their time to *only* delivering the new counselling service. In the designated approach (MIND_DES), CHWs already working in the facility will be designated to deliver the service *in addition* to their other chronic disease-related activities such as adherence counselling for HIV and health promotion. Supervision and debriefing of all the counsellors in the active arms will be task-shifted to registered psychological counsellors in line with the national mental health policy framework.^27^ Descriptions of the CHWs and registered psychological counsellors roles in the MIND-DED and MIND-DES models and their qualifications and skills levels are detailed in the trial protocol.^24^

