#### Sample size and patient population

Recruitment will be restricted to consenting adult patients who meet criteria for hazardous alcohol use or depression using the AUDIT or CES-D. These patients are already diagnosed and receiving treatment for diabetes or HIV, but not currently receiving treatment for a CMD. The trial requires a sample size of 1200 patients (600 with HIV and 600 with diabetes) to detect reductions in hazardous alcohol use and risk of depression at 12-month follow-up. The sample size calculations are based on a cluster randomised design with two active arms and a control arm. This clinical trial is powered to detect clinical outcomes, specifically reductions hazardous/harmful alcohol use and risk of depression at 12-month follow-up rather than economic outcomes.^24 35^

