Establishing the use of referral services is challenging given that there is no health information system that enables patient pathways through care to be established. Therefore, to establish patient utilisation of health services beyond their HIV and diabetes care at the primary level, we will administer a patient questionnaire developed for the study at baseline, and at the 6-month and 12-month assessments. Using this questionnaire, we will capture health service utilisation for other primary care services (eg, TB treatment), hospital services, emergency department care, paramedic care and referrals to mental health providers. Patients will be asked to quantify the number of these additional visits, and lengths of stay in hospital. Given concerns with patient recall, we have asked patients to estimate their usage of ambulatory services over the previous month and have used a recall period of 6 months for inpatient services. These data will then be extrapolated to estimate costs over the time horizon.

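### The incremental cost is described only as a difference in mean costs, with no adjustment for the service use and patient costs collected at baseline, so the questionnaire-based cost components are estimated less precisely than they could be

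*Protocol article*

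**What the plan says.** The protocol article, under Statistical analysis of costs and effects, gives the cost comparison in three steps. Mean provider and patient costs are computed; then "Cost differences between the MIND-TAU, and the MIND-DES and MIND-DED alternatives will be calculated"; then sampling uncertainty is handled by unnamed methods suited to non-normal costs. No covariate and no clinic term is named. Effects are given a linear regression in which arm is the only term named.

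Resource use is measured before the intervention as well as after it. For provider costs, Measurement of resource use says "we will administer a patient questionnaire developed for the study at baseline, and at the 6-month and 12-month assessments". This questionnaire covers services outside HIV and diabetes primary care, such as TB treatment, hospital, emergency and mental health referral. On its recall windows, the article says "we have asked patients to estimate their usage of ambulatory services over the previous month and have used a recall period of 6 months", the longer window applying to inpatient care. For the patient perspective, the section of the same name says "we will use a questionnaire at baseline, 6 and 12 months to estimate resource use".

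The trial is "a cluster randomised controlled trial across 24 public primary care facilities", with three arms and 1200 patients. The article does not say what role the baseline answers play in the cost comparison.

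**The concern.** The incremental cost is the numerator of every ICER, and one stated objective is to estimate cost offsets in referral care, including TB, emergency and inpatient care. Those offsets come from the patient questionnaire. Patients who used more care before enrolment can be expected to use more afterwards, and with few clinics per arm the arms can differ by chance in prior use. A plain difference in means leaves that variation in the estimate, although the variable that would remove part of it has been collected.

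What is at stake is precision: the interval for the cost offset is wider than it need be, and so is the uncertainty shown in the acceptability curve. This matters somewhat more here because, in the article's words, "This clinical trial is powered to detect clinical outcomes", not economic ones.

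**Working it through.** No figure in the article bears directly on this point, so there is none to reproduce. The article gives no ICC for costs and no correlation between baseline and follow-up cost. Both are assumed below and shown as ranges.

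**Inputs from the article:** 24 facilities, three arms, 1200 patients. **Assumed:** an equal split, so 24/3 = 8 clinics per arm, 1200/24 = 50 patients per clinic and 1200/3 = 400 patients per arm.

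**Step 1: chance imbalance between two arms, in patient SDs.** SE = sqrt(2 × [1 + 49 × ICC] / 400).
- ICC 0.01: sqrt(2 × 1.49/400) = 0.086
- ICC 0.02: sqrt(2 × 1.98/400) = 0.099
- ICC 0.05: sqrt(2 × 3.45/400) = 0.131
- ICC 0.10: sqrt(2 × 5.90/400) = 0.172

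**Step 2: carry-over into the cost difference.** With correlation ρ between baseline and follow-up cost, a one-SE baseline imbalance moves the unadjusted difference by ρ × SE. For ρ = 0.3 to 0.5 this is 0.030 to 0.050 SD at ICC 0.02, and 0.039 to 0.066 SD at ICC 0.05.

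**Step 3: precision under normal theory.** The ratio of adjusted to unadjusted interval width is sqrt(1 − ρ²), taking the same ρ within and between clinics. It is 0.954 at ρ = 0.3 and 0.866 at ρ = 0.5.

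**Step 4: precision with skewed costs.** Lognormal costs were simulated (log variance 1, 8 clinics of 50 patients in each of two arms, no true difference, 4000 replicates). Here ρ is the correlation on the log scale. The plain difference in means was compared with a linear model containing arm and baseline cost.

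| ICC | ρ (log scale) | SD unadjusted | SD adjusted | Ratio |
|---|---|---|---|---|
| 0.02 | 0.3 | 0.193 | 0.187 | 0.967 |
| 0.02 | 0.5 | 0.191 | 0.175 | 0.915 |
| 0.05 | 0.3 | 0.239 | 0.231 | 0.968 |
| 0.05 | 0.5 | 0.239 | 0.212 | 0.887 |

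The gain is therefore about 3% at ρ = 0.3 and 8% to 11% at ρ = 0.5. It is smaller than in Step 3 mainly because a log-scale ρ is a lower correlation on the cost scale. With log variance 1 it becomes (e^ρ − 1)/(e − 1): 0.350/1.718 = 0.20 for ρ = 0.3 and 0.649/1.718 = 0.38 for ρ = 0.5. Both estimators were centred close to the true difference of zero (means within 0.01).

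**Step 5: dilution in total provider cost.** Only part of the total has a baseline counterpart. Suppose the questionnaire components supply a share f of the variance of the total cost difference, independently of the rest. The ratio R from Step 4 then becomes sqrt(1 − f × [1 − R²]). As an illustration with f = 0.5:
- R = 0.967 gives sqrt(1 − 0.5 × 0.065) = 0.984
- R = 0.887 gives sqrt(1 − 0.5 × 0.213) = 0.945

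The gain for the total would then be roughly 2% to 5%. The share f is not known from the article.

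**The case against.** The strongest reply is that the article does not call the difference raw or unadjusted. Its open wording on methods for non-normal costs could include a regression with covariates, and an article commonly leaves a covariate list to the full analysis plan. This stands in part. An unadjusted analysis is the plain reading of the text, not a stated commitment. But this article is itself the protocol of the economic evaluation. The cited section is where the estimate of incremental cost is defined, and its only further cost method concerns sampling uncertainty, not the estimate. Naming a better estimator that uses data already in hand is more than asking for omitted detail.

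The second reply is that costs are not treated worse than effects, because a regression on arm alone is also a difference in means. That is correct, and the point does not rest on the contrast.

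The third reply concerns reach, and it stands. The baseline data are a one-month ambulatory and a six-month inpatient window, not a full history. Intervention costs have no pre-enrolment counterpart. HIV and diabetes service costs come from step-down costing and treatment guidelines applied to facility statistics, so they have no patient-level baseline either. A one-month snapshot may correlate only modestly with 12-month cost, which would put the gain at the low end.

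The fourth reply also stands: chance imbalance is part of the sampling error that a correct interval already covers, so imbalance and lost precision are one harm, not two.

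**Conclusion.** The point holds as a matter of efficiency for the questionnaire-measured components: referral, hospital and patient costs. Under an equal split, log-scale correlations of 0.3 to 0.5 and ICCs of 0.02 to 0.05 with skewed costs, adjustment narrows their intervals by about 3% to 11%, and the interval for total provider cost by less. All of these inputs except the 24 facilities, three arms and 1200 patients are assumed.

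A reader might infer three stronger claims, none of which the article supports.
- **Bias.** Under randomisation the unadjusted difference is unbiased.
- **A distortion of up to about a third of mean cost.** That figure needs the top of every assumption at once: 0.172 × 0.6 × 3 = 0.31, from ICC 0.10, correlation 0.6 and a cost SD three times the mean. It also applies the correlation to total cost, most categories of which have no patient-level baseline measure.
- **Baseline answers counted in the costs.** The provider section says that reported use will be extrapolated over the time horizon and does not separate the assessment rounds. That silence does not show that pre-enrolment use enters the costed period.

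**What to change.** In Statistical analysis of costs and effects, state that:
- arm differences in patient-reported service-use costs and in patient costs are estimated by regression on arm plus the patient's own baseline value, with baseline use valued at the same unit costs as follow-up use;
- the model is on the natural cost scale, with an interval that allows for skewness and for randomisation by clinic;
- the adjusted difference enters the ICER, and the unadjusted difference in means is reported as a sensitivity analysis;
- intervention costs and step-down HIV and diabetes costs are added without this adjustment.

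The cost is a few sentences of analysis wording. No new data are required, and missing baseline values can be handled by the multiple imputation already planned as the base case. Fixing the choice in advance also prevents a later choice between adjusted and unadjusted ICERs once the results are known.

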**Methods and analysis:**

This evaluation will be conducted as part of a three-armed cluster randomised controlled trial of clinical effectiveness. Trial clinical outcome measures will include primary outcomes for risk of depression and alcohol use, and secondary outcomes for risk of chronic disease (HIV and diabetes) treatment failure. The cost-effectiveness analysis will evaluate cost per unit change in Alcohol Use Disorder Identification Test and Centre for Epidemiological Studies scale on Depression scores as well as cost per unit change in HIV RNA viral load and haemoglobin A1c, producing results of provider and patient cost per patient year for each study arm and chronic disease. The cost utility analyses will provide results of cost per quality-adjusted life year gained. Additional analyses relevant for implementation including budget impact analyses will be conducted to inform the development of a business case for scaling up the country’s investment in mental health services.

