#### Sensitivity analyses

The decision analytical models will allow for univariate and multivariate sensitivity analyses to be conducted. This will enable the robustness of study findings to be tested by varying key parameters such as utilisation rates and assessing the impact on cost-effectiveness results. Standard areas of analytical focus will be considered, including testing sensitivity around the resource cost and prices, and theoretical controversies,^49^ for example, TTO weights^50^ and discounting of outcomes.^36^ Further analyses to inform the economics of task-sharing will include sensitivity analysis focused on economies and diseconomies of scale and scope, using detailed data from the TMT.^51^ This will include testing variations in staff hours worked, variations in staff mix, lay counsellor funding models and infrastructure investments. The impact of intervention dosage on outcomes will also be assessed in the sensitivity analyses. Statistical methods including multiple imputation will be used to manage the effect of missing information on costs and effects.^52^ These sensitivity analyses are summarised in table 2. Probabilistic sensitivity analysis (which allows application of CIs to point estimates) will be used for sensitivity analyses of all relevant individual-level variables. The sensitivity analyses will be used to produce a cost-effectiveness acceptability curve.

**Table 2 T2:** Planned sensitivity analyses

	Base case	Range
Simple sensitivity analysis		
Discount rate	3%	0%–10%
QALYs: HRQoL weights	EQ-5D valued using UK TTO	EQ-5D valued using Zimbabwe TTO
Unit costs	Primary data and data from published sources and official statistics for South Africa	Varied within plausible ranges as determined from a literature review of South African cost studies
Missing data	Multiple imputation	Complete case analysis
Probabilistic sensitivity analysis		
Intervention utilisation data	Mean value	95% uncertainty interval
Referral service utilisation data	Mean value	95% uncertainty interval
EQ-5D/CES-D/AUDIT data	Mean value	95% uncertainty interval
Clinical outcomes (HbA1c, HIV-1 RNA)	Mean value	95% uncertainty interval

AUDIT, Alcohol Use Disorder Identification Test; CES-D, Centre for Epidemiological Studies scale on Depression; EQ-5D, EuroQol-5D; HbA1c, haemoglobin A1c; HRQoL, health-related quality of life; QALY, quality-adjusted life year; TTO, time trade-off.

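### The stated effect model regresses on arm alone although 24 facilities were randomised, so intervals for the effects would be too narrow, and the cost and uncertainty text does not provide for clustering

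*Protocol article*

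**What the plan says.** The abstract calls the parent study a "three-armed cluster randomised controlled trial of clinical effectiveness", and Trial design in the protocol article gives 24 facilities as its setting. Sample size and patient population carries the design into the planning: "The sample size calculations are based on a cluster randomised design with two active arms and a control arm".

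Statistical analysis of costs and effects then names one model for all effects, including the QALY: "Effect in terms of CES-D, AUDIT, HIV viral load, HBA1c and the QALY will be analysed using linear regression on intervention type". For costs, the same section promises "statistical methods that account for the non-normal distribution of costs".

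Under Sensitivity analyses, the probabilistic analysis "will be used for sensitivity analyses of all relevant individual-level variables". Table 2 lists the inputs as mean values with 95% uncertainty intervals. Multiple imputation is the base case for missing data, and the sensitivity analyses lead to an acceptability curve. None of these sections mentions facility effects, clustered standard errors, resampling of facilities, or the correlation between a patient's cost and effect.

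**The concern.** Patients of one facility share counsellors, management and a local population, so their outcomes tend to be correlated. When facilities are randomised, that correlation adds directly to the variance of every comparison between arms. A regression whose only named regressor is the arm treats about 1200 patients as independent. It reports a precision that 24 randomised units cannot give.

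The sample size allowed for this and the stated analysis does not. The article means to inform decision makers and support a business case for scale-up. The output most exposed is the stated probability that an arm is cost-effective, because it depends on the spread of the estimates as well as on their centre.

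**Working it through.** **Inputs from the protocol article.** 24 facilities and three arms (abstract; Trial design); 1200 patients, 600 with HIV and 600 with diabetes (Sample size and patient population).

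**Assumptions.** The article gives no ICC, so 0.01, 0.02 and 0.05 are used as a range. Facilities are taken to be of equal size. The planned 1200 cannot be reproduced, because no effect size, standard deviation, ICC, error rate, power or dropout is given. It is not disputed here.

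**Average cluster size.** m = 1200 / 24 = 50. For outcomes measured in one disease group only (HbA1c, viral load), m = 600 / 24 = 25.

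**Formulas.**
- Design effect: DE = 1 + (m − 1) × ICC.
- Factor by which the unadjusted standard error is too small: √DE.
- True coverage of a nominal 95% interval: 2Φ(1.96 / √DE) − 1.

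**All patients, m = 50.**

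| ICC | DE | √DE | 1.96 / √DE | Coverage |
|---|---|---|---|---|
| 0.01 | 1 + 49 × 0.01 = 1.49 | 1.22 | 1.61 | 89% |
| 0.02 | 1 + 49 × 0.02 = 1.98 | 1.41 | 1.39 | 84% |
| 0.05 | 1 + 49 × 0.05 = 3.45 | 1.86 | 1.06 | 71% |

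Equivalently, a nominal 5% test has a true size of about 11%, 16% and 29%.

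**One disease group, m = 25.**

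| ICC | DE | √DE | Coverage |
|---|---|---|---|
| 0.01 | 1 + 24 × 0.01 = 1.24 | 1.11 | 92% |
| 0.02 | 1 + 24 × 0.02 = 1.48 | 1.22 | 89% |
| 0.05 | 1 + 24 × 0.05 = 2.20 | 1.48 | 81% |

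**Small number of facilities.** With 24 − 3 = 21 degrees of freedom, the t multiplier is 2.08 instead of 1.96. A correct interval at m = 50 is then √DE × 2.08 / 1.96 = 1.30, 1.49 and 1.97 times as wide as the unadjusted one.

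**Acceptability curve.** Suppose that net benefit is roughly normal, has the same ICC, and shows an unadjusted probability of cost-effectiveness of 0.95, so z = 1.645. The corrected probability is Φ(1.645 / √DE), which at m = 50 is 0.91, 0.88 and 0.81. This illustrates the size and does not forecast this trial's curve.

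**The case against.** The strongest reply is that this is a condensed article. The trial's own protocol, which is cited but not shown, may specify a clustered model. The section Estimating intervention effects says that effectiveness comes from the trial, and one short sentence does not exclude robust standard errors or a random effect. That would answer a complaint about missing detail. It does not answer this one, because the article sets its own model for these effects, the QALY among them, and the model as worded does not fit the design. If a clustered model is fixed elsewhere, the sentence disagrees with it and still needs correcting.

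Several parts of the other side do stand:

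- **Costs.** A reader might infer that costs are corrected for skewness and nothing else. The text does not say so: "Sampling uncertainty for cost data will be estimated using statistical methods that account for the non-normal distribution of costs" is compatible with a clustered method. The fair statement is that clustering is not provided for.
- **Probabilistic analysis.** A reader might infer from Table 2 that inputs are varied singly. The section also mentions multivariate analyses, and a table with one row per input does not settle the matter. Cost-effect correlation is simply not addressed.
- **Strength of clustering in costs.** A reader might expect it to be especially strong, with an ICC near 0.10, because some unit costs use facility expenditure and headcount. The documents do not establish this. Table 1 also uses arm-level headcounts, national tender prices and national laboratory prices, patient time is valued at one survey-wide average, and it is not stated whether facility unit costs are applied by facility or averaged.
- **Relevance of test size.** The decision rule compares a ratio with a threshold, and the trial is not powered for economic outcomes. Coverage and the curve are therefore the more useful measures.

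**Conclusion.** The point holds for the effect model, which is stated and does not respect randomisation by facility. The direction is certain for any positive ICC. The size rests on assumed ICCs of 0.01 to 0.05 and equal facility sizes: standard errors too small by 1.22 to 1.86 times for outcomes measured in all patients, and by 1.11 to 1.48 times for HbA1c and viral load.

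For costs, imputation and the probabilistic analysis, the conclusion is weaker: the text does not provide for clustering or for cost-effect correlation. It would go too far to say that these steps ignore clustering or that every interval is bound to be wrong. What follows is conditional: a curve drawn from estimates that lack facility-level variance would be too confident. Clustering mainly affects uncertainty, so the ratios themselves change little.

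**What to change.** Replace the sentence on the effect model with wording such as:

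*Costs and effects will be analysed together at patient level, allowing for clustering by facility and for the correlation between cost and effect, with a small-sample correction for 24 facilities.*

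Then name the method. Two options would serve:

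- a two-stage bootstrap that resamples facilities within arm and then patients within facility, keeping each patient's cost and effect together, which also copes with skewed costs; or
- a bivariate multilevel model with facility as a random effect and a suitable cost distribution.

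Include facility in the multiple imputation model. Draw the probabilistic sensitivity analysis and the acceptability curve from the resulting joint estimates. If the trial protocol already fixes a clustered model for CES-D and AUDIT, refer to it and keep the two consistent.

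The cost is wider intervals and a little more programming. No new data are needed.

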### MIND economic evaluation

#### Objective

The study will be a prospective economic evaluation. The objectives include estimating:Full economic provider costs of the mental health intervention; any cost offsets attributable to the intervention related to changes to the costs of HIV or diabetes care at the primary care level and changes to the costs of referral care (including tuberculosis (TB), emergency department and inpatient care).Patient costs: associated with the intervention which will include direct out-of-pocket payments to private health providers (consultations and medications, etc), travel and subsistence costs and productivity losses.Cost-effectiveness in terms of the incremental cost per unit of improvement in disease-specific outcome (CES-D, AUDIT, HIV-1 RNA, HbA1c).Cost-utility in terms of the incremental cost per quality-adjusted life year (QALY) gained.Budget impact of scaling up the intervention.

To achieve these objectives, the incremental cost-effectiveness ratio (ICER) will be calculated by ordering the MIND_DED, the MIND_DES and MIND_TAU alternatives from least cost to highest cost and calculating the difference in costs and outcomes against the next less costly, non-dominated alternative or against the common baseline of MIND_TAU.

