#### Determining cost-effectiveness

The analysis will be conducted in line with the Consolidated Health Economic Evaluation Reporting Standards guidelines.^47^ Decision analytical models^37^ integrating the cost and outcomes of the different intervention alternatives will be developed to assess cost-effectiveness. As a meaningful impact of the MIND-DES and MIND-DED on both costs and effects is anticipated, ICERs will be estimated in terms of incremental cost per natural unit and/or intermediate outcome for the CEA, and incremental cost per QALY gained for the CUA. As the trial is focused on health systems strengthening for the delivery of mental health services, the decision rule applies to maximising health within the healthcare budget constraint. Therefore, ICERs will be calculated from the provider perspective and, the cost per QALY gained will be compared with the cost-effectiveness thresholds (CETs) for LMIC settings.^48^ If our intervention’s ICER is less than the chosen CET, this will mean that diverting resources to the intervention will increase population health, and if the ICER is more than the CET the intervention is not cost-effective. Patient costs will be collected and reported on separately. In addition, to satisfy the requirements of common guidelines^47^ and to allow for some degree of comparability with other studies, the ICERs will also be presented for the societal perspective, that is, including both provider and patient costs.

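### HIV viral load is fixed as linear regression and cost per unit change with no scale named; in untransformed copies/mL, a few very high values would dominate the HIV-specific ICER

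*Protocol article*

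**What the plan says.** Under Statistical analysis of costs and effects, the article puts viral load in one list with CES-D, AUDIT, HbA1c and the QALY: "HIV viral load, HBA1c and the QALY will be analysed using linear regression on intervention type". Shortly before, for costs alone, it writes: "Sampling uncertainty for cost data will be estimated using statistical methods that account for the non-normal distribution of costs".

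The effect measure for the cost-effectiveness analysis is given in three places:
- Abstract, Methods and analysis: "cost per unit change in HIV RNA viral load and haemoglobin A1c".
- Objective: "incremental cost per unit of improvement in disease-specific outcome (CES-D, AUDIT, HIV-1 RNA, HbA1c".
- Determining cost-effectiveness: "incremental cost per natural unit and/or intermediate outcome for the CEA".

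In Table 2 (Sensitivity analyses), the row "Clinical outcomes (HbA1c, HIV-1 RNA" has the mean as base case and a 95% uncertainty interval as range, with no alternative scale or threshold. No section mentions log10, a suppression cut-off, a detection limit, or what one unit of viral load is.

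The Abstract describes the secondary outcomes as the risk that HIV or diabetes treatment fails. Sample size and patient population says participants are already being treated for their chronic disease.

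**The concern.** In people already on HIV treatment, one expects many values at or near the detection limit and the rest spread over several orders of magnitude; the article gives no distribution. A linear regression of such values on arm estimates a difference in arithmetic means, and on the copies/mL scale that mean is largely set by the few highest values. The authors allow for skewness in costs but say nothing of it for this outcome.

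Viral load is one of four named disease-specific ICERs and the only one specific to HIV. If its denominator is a mean difference in copies/mL, a real gain in suppression could be lost in noise or show as harm, and a cost per copy/mL tells a health service little. If log10 was meant, most of the power problem goes away, but the ICER unit is still undefined and the scale could be chosen after the data are seen.

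**Working it through.** **The plan's own figure.** The article gives no power or precision figure for viral load. The 1200 is set for alcohol use and depression risk; only the sum 600 + 600 = 1200 can be checked, because alpha, power, effect size, SD, ICC and dropout are not given.

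**Inputs from the article.** "600 with HIV and 600 with diabetes"; "two active arms and a control arm"; 24 facilities.

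**Assumptions.**
- Equal allocation: 600/3 = 200 HIV patients per arm, 24/3 = 8 facilities per arm, 600/24 = 25 HIV patients per facility.
- Two-sided alpha 0.05.
- Suppressed patients at 20 to 50 copies/mL.
- Unsuppressed log10 values normal with mean 4.3, limited to 3 to 7; SD varied.

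**Step 1: proportion unsuppressed, by formula.** With n = 200 per arm, power = Φ[(d − 1.96·√(2p̄(1−p̄)/n)) / √((p0(1−p0)+p1(1−p1))/n)].
- 30% v 20%: (0.10 − 1.96 × 0.0433)/0.0430 = 0.35, power 64%.
- 40% v 28%: (0.12 − 1.96 × 0.0474)/0.0470 = 0.58, power 72%.
- 20% v 12%: (0.08 − 1.96 × 0.0367)/0.0364 = 0.22, power 59%.

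The chance of a wrong sign is Φ(−d/SE): Φ(−2.33) = 1.0%, Φ(−2.55) = 0.5% and Φ(−2.20) = 1.4%.

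**Step 2: why raw copies do worse.** Treat suppressed values as zero and ignore the limits on the log10 values. The ratio of difference to standard error on raw copies is then (p0 − p1) / √{[(p0 + p1)E − p0² − p1²]/n}, with E = exp[(2.303·SD)²]. For 30% v 20%:
- SD 0.4: E = 2.34, ratio = 0.10/√(1.038/200) = 1.39, against 2.33 for the proportion.
- SD 0.9: E is about 73, and the ratio falls to about 0.23.

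This shows the mechanism only. The limits and the non-normality matter at wide spreads, so the power figures come from simulation.

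**Step 3: simulation, 30% v 20%, 200 v 200, no clustering.**

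| Unsuppressed log10 SD | Raw copies/mL | log10 | Proportion | Share of control-arm total held by top 5% |
|---|---|---|---|---|
| 0.4 | 32% | 62% | 63% | 47% |
| 0.6 | 17% | 62% | 64% | 63% |
| 0.8 | 10% | 60% | 64% | 77% |
| 1.0 | 7% | 59% | 65% | 85% |

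**Step 4: all three pairs, SD 0.4 to 0.9.** Raw power is about 7% to 35%, log10 52% to 71%, proportion 58% to 72%. The raw difference points the wrong way in 7% to 30% of runs.

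**Step 5: sensitivity.**
- Larger effect: 30% v 15% gives raw power of 65% at SD 0.4 and 15% at SD 1.0, against 92% to 95% on log10 and 95% to 96% for the proportion.
- Clustering: the design effect is 1 + 24·ICC, which is 1.24 at ICC 0.01 and 2.2 at ICC 0.05. For 20% v 10% at SD 0.8, going from ICC 0.01 to 0.05, raw power goes from 13% to 9%, log10 from 68% to 43%, and the proportion from 71% to 47%. All three fall; the order does not change.

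**The case against.** The strongest reply is that the article never says copies/mL. Linear regression suits log10 viral load equally well, the unit is left open, and the ICER may be per natural unit or intermediate outcome, which could include suppression. On log10 the loss against the proportion is only about 0 to 6 points. This stands: everything said about dominance by extreme values is conditional on the raw scale.

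Second, scale and detection-limit handling are often left to an analysis plan, and the parent trial is described in another paper. That would answer a complaint of missing detail. It does not fully answer this point, because the article fixes the model, the per-unit ICER and the mean as base case, and shows concern about skewness for costs only.

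Third, viral load is a secondary outcome, no power is claimed for it, the threshold comparison uses cost per QALY, and the probabilistic analysis would show a wide interval. All of this stands and limits the consequence. It does not make the raw mean a good denominator.

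A reader might go further and infer that the HIV result will have almost no power or will be noise. The documents do not support that. They give no suppression rate, distribution, effect size, alpha or ICC, and at SD 0.4 raw power reaches 32% in the main scenario and 65% with a larger effect.

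**Conclusion.** The point holds in conditional form. The article commits viral load to linear regression and a cost per unit change without naming a scale, a suppression endpoint or a treatment of values at the detection limit. If copies/mL are used, roughly half or more of the power available on log10 or the proportion suppressed is lost in the three main scenarios, and a true benefit can appear with the wrong sign. The direction held in every scenario tried. The size depends mainly on the spread of unsuppressed values, which is assumed, as are the suppression rates, equal allocation and alpha; the main figures also ignore clustering. What is affected is one secondary, HIV-specific ICER, not the primary outcomes or the cost-per-QALY decision.

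**What to change.** Define the HIV effect in the cost-effectiveness analysis as the proportion virally suppressed at 12 months, at the trial's own cut-off, with the ICER as cost per additional patient suppressed. This fits the Abstract's framing in terms of treatment failure. Support it with log10 viral load, allowing for values below the detection limit. Adjust both for the baseline value and account for clustering by facility. Replace the per-unit wording for HIV RNA in the Abstract and Objective, and change the HIV-1 RNA entry in Table 2 to match.

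The change is to wording and analysis only and uses the same assay data. Dichotomising loses some detail, which the log10 analysis covers.
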